### Objectives and hypotheses

In line with our rationale, the objectives of the present pilot clinical study are to: 1) examine the safety, feasibility and effectiveness of CIMT paired with tDCS targeting PMC, versus CIMT delivered alone in alleviating impairments of the paretic hand in patients with chronic stroke; and 2) assess neural markers associated with response to paired paradigm versus CIMT alone.

We hypothesize that the paired approach involving stimulation of PMC in the stroke-affected hemisphere will be more effective than CIMT in improving hand function in chronic stroke. The paired approach will facilitate the individual’s specific neural substrates of recovery and will be safe to employ throughout the length of the study.

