## Methods

### Study design

We use a pilot, randomized, sham-controlled, double-blind clinical study design. Twenty patients are being randomly assigned to PMC tDCS plus CIMT or sham tDCS plus CIMT groups. All outcomes are collected at pretest and at post-test after 5 weeks of intervention. At 3-month follow up, outcomes of hand function are collected to examine retention.

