### Randomization

We are using randomization blocks in sizes of four, where two patients in a block are assigned to PMC tDCS plus CIMT and the other two to the sham tDCS plus CIMT group. Such block randomization prevents the possibility that several patients in a row would get randomized to tDCS or sham tDCS groups in the early part of the study. The order of patients in blocks is random, generated using an online tool. Allocations are concealed in an opaque envelope and hidden in a locked cabinet with restricted access; they are opened by an investigator not involved in data collection or analysis before the first day of treatment.

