### Safety

A report on side effects is completed at every visit. At every treatment visit, the report documents whether or not subjects experienced side effects related to tDCS, such as tingling, headache, itching, fatigue, pain and problems concentrating. On days of testing with TMS, the report also documents whether subjects experienced side effects related to TMS, such as seizure, loss of consciousness or hearing difficulties. Transient side effects are documented separately from serious events that are categorized as related or unrelated to interventions. Serious adverse events include those that may require inpatient hospitalization. Adverse event reporting follows guidelines set by the local Institutional Review Board. To ensure safety in case of seizure or any unrelated serious medical issues, provisions include an on-call medical response team and clinical research nursing support that work closely with the physician on the study (AM).

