### Sample size estimation

The sample size has been estimated based on previous studies that have paired invasive or noninvasive stimulation with rehabilitation
[8,9,12,17,31]. Because UEFM has been most commonly investigated across the majority of studies, we used the effect sizes calculated across these studies to generate several permutations of sample size and the corresponding extent of change in the UEFM score (Figure 
2) to estimate power. Using a method of simulations
[63] where 500 simulations were performed, we estimated sample sizes that would generate significant differences upon the UEFM based on a mixed-effects model. From this method, we have found that a sample size of 10 per group would yield 83% power (95% CI 79.41 to 86.19%) to detect differences between groups (PMC tDCS plus CIMT sham tDCS plus CIMT group), 99.6% power to note differences across time (95% CI 98.56 to 99.95%) and 97% power (95% CI 95.35 to 99.46%) to observe a group X time interaction (Figure 
2).

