**Figure 2 F2:**
[figure not shown]
**Power analysis: power was determined by simulation.** Lower and upper lines define exactly the 95% CI for power, calculated based on the binomial distribution. N is the total sample size. The analysis was performed at a 0.05 significance level considering 2 × 2 factorial analysis of variance (ANOVA) (tDCS plus CIMT and sham tDCS plus CIMT from pretest to post-test). Power has been estimated here for an interaction term (A *C).

Although the estimated sample size appears small, it is commensurate with the pilot exploratory nature of our study. Pilot studies involving brain stimulation generally use smaller sample sizes compared to rehabilitation trials
[28] because contraindications to brain stimulation/imaging are constraining. Still, we anticipate having adequate statistical power based on prior evidence where despite enrolling a total of 14 to 30 subjects, several studies report significant benefit of adjunctive stimulation
[8,30,44]. Additionally, use of a repeated-measures design further provides greater power. Studying neural mechanisms with fMRI and tractography in limited sample sizes is challenging. Given the exploratory nature of our pilot study, we would be able to highlight elemental neural mechanisms of recovery. Previously, in a three-group, randomized controlled study design with a small sample of 20, we deciphered correlates of fMRI
[37]. Recently too, Stagg *et al*.
[64] show differences in fMRI activation across varying types of tDCS interventions in 11 patients with stroke. Without overemphasizing the importance of small pilot studies, we stress instead the significance of large-scale studies in generating clear evidence of efficacy. Our current pilot exploratory study is a step in that direction as it would offer estimates of effect size related to PMC tDCS and neural markers that can serve as entry criteria.

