### Statistical and data analyses

Feasibility: analysis of feasibility includes investigating the rigor of experimental blinding and determining compliance with the 5-week outpatient rehabilitation program. A chi-square analysis will determine whether patients in one group versus another estimate their group assignment correctly. Investigators also complete a similar questionnaire at the end of the study. While patient responses will indicate the rigor of the blinding procedures, responses from investigators will ensure investigator equipoise, preventing observer bias. Attrition or missing data will be analyzed using a strategy known as multiple imputations
[65], where each missing value is replaced with a set of plausible values that represent the uncertainty about the true value. The multiple imputed data sets are analyzed using standard procedures used for complete datasets and by combining results from these analyses. The method of multiple imputations does not attempt to estimate each missing value through simulated values, but rather represents a random sample of missing values. This process results in valid statistical inferences that properly reflect the uncertainty due to missing values.

Safety: the incidence of adverse events in each group will be computed as a proportion of individuals in each group who experienced side effects. We will be using the Fisher exact test to contrast the incidence of side effects between both groups.

Efficacy and markers of recovery: our primary endpoint of efficacy is the UEFM. Secondary outcomes include nine-hole peg test, Action Research arm test, motor activity log, finger abduction strength and the modified Ashworth scale of spasticity. A general linear mixed-model approach will be followed to analyze functional outcomes across three levels of time (pre, post, and follow-up). Significant two-way interaction, whenever present, will be explored using the Tukey honestly significant difference (HSD) test. Non-parametric tests will be used if the distribution is not normal.

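### The stated safety comparison uses only whether a patient was affected, dropping the visit-by-visit side-effect record and leaving little basis for judging the safety hypothesis

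*Protocol article*

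**What the plan says.** Safety is part of the first objective, and the hypothesis says of the paired approach that it "will be safe to employ throughout the length of the study" (Objectives and hypotheses).

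On collection, the Safety section says: "At every treatment visit, the report documents whether or not subjects experienced side effects related to tDCS". It lists tingling, headache, itching, fatigue, pain and problems concentrating. Serious events are documented apart from transient ones and classed as related or unrelated. The CIMT section gives 15 clinic visits over 5 weeks. The tDCS section says that sham patients receive 1 mA for 30 to 60 seconds at outset, and that current is ramped up slowly in all patients.

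On analysis, Statistical and data analyses fixes the measure, "the incidence of adverse events in each group will be computed as a proportion of individuals in each group who experienced side effects", and the test: "We will be using the Fisher exact test to contrast the incidence of side effects between both groups". The Abstract also names the Fisher test. No safety event rate, acceptable margin or safety power is given, and no separate analysis of serious events is described.

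**The concern.** The measure and the test are both stated, so this is a choice the article makes and not a detail left to another document. A proportion of individuals affected counts each patient as yes or no. The article does not say whether the side-effect types are pooled, but on either reading the number of visits affected is dropped. One mild tingle on the first day counts the same as a headache at every visit.

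Two features make the yes/no measure a weak discriminator here. Fifteen visits give each patient many chances to report a mild effect at least once. The sham also delivers current at onset, and tingling is on the list. If most sham patients are affected at some point, there is little room for the active arm to look worse.

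The hypothesis concerns safety over the whole study, and the pilot is meant to inform later trials. A finding of no significant difference from an insensitive comparison would be easy to carry forward as reassurance.

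**Working it through.** **Inputs from the article.** Sample size: "Twenty patients are being randomly assigned to PMC tDCS plus CIMT or sham tDCS plus CIMT groups". Allocation: "two patients in a block are assigned to PMC tDCS plus CIMT and the other two to the sham tDCS plus CIMT group", hence 10 per arm. Treatment visits: 15 (CIMT section). The only significance level is the one given for the UEFM power analysis: "The analysis was performed at a 0.05 significance level".

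**Assumptions.** Two-sided 0.05 for the safety test; per-visit side-effect rates; within-patient correlation. The article gives none of these for safety, so ranges are shown.

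**The plan's own figure.** Power is stated only for the UEFM. The printed interval for 83% (79.41 to 86.19%) is the exact binomial interval for 415 of 500 simulations. The power itself cannot be recomputed, because the effect size and SD are not in the text. There is no safety figure to reproduce.

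**Step 1: what the Fisher test needs at 10 v 10.** No event rate has to be assumed here. Against 0/10 affected, significance needs 5/10 (p = 0.033; 4/10 gives p = 0.087). Against 1, 2 or 3 affected it needs 7, 8 or 9. Against 4 or 5 it needs 10. If 6 or more sham patients are ever affected, no result in the active arm can show an excess (10 v 6 gives p = 0.087).

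**Step 2: proportion ever affected, independent visits.** With per-visit rate p, the proportion is 1 − (1 − p)^15. For example, 1 − 0.9^15 = 79% and 1 − 0.8^15 = 96.5%. Exact Fisher power sums the binomial probabilities of all significant tables.

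| Per-visit rates | Ever affected | Fisher power |
|---|---|---|
| 1% v 2% | 14% v 26% | 2.3% |
| 2% v 4% | 26% v 46% | 5.4% |
| 5% v 10% | 54% v 79% | 9.5% |
| 10% v 20% | 79% v 96.5% | 2.6% |
| 20% v 40% | 96.5% v 100% | 0% |

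**Step 3: allowing for clustering within patients.** Each patient's rate is drawn from a beta distribution with mean p and parameters pk and (1 − p)k, where k = (1 − ρ)/ρ and ρ is the within-patient correlation. There were 2,000 simulated trials per setting. Cells show power (%) of Fisher on ever/never, then of a Mann-Whitney test on the number of visits with the event (0 to 15).

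| ρ | 2% v 4% | 5% v 10% | 10% v 20% | 20% v 40% |
|---|---|---|---|---|
| 0 | 6 / 13 | 10.5 / 32 | 2 / 60 | 0 / 95 |
| 0.1 | 3 / 9 | 7 / 18.5 | 10.5 / 34 | 0.6 / 62 |
| 0.3 | 1 / 4 | 4 / 12 | 8 / 21 | 10 / 38 |
| 0.5 | 0.3 / 2 | 3 / 8 | 6 / 15 | 10 / 26 |

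Fisher never exceeds about 11%, and the rank test is higher in every cell. Repeat simulations at ρ = 0.3 gave 19 to 21% for the rank test at 10% v 20% and 34 to 38% at 20% v 40%, so about 20% and about 35% are fair summaries. With equal rates in the two arms the rank test rejected in at most 5% of trials.

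**Step 4: serious events.** With 0 events in 10 patients, the two-sided 95% upper limit is 1 − 0.025^(1/10) = 30.8%.

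**The case against.** The strongest reply is that a patient-level proportion with Fisher's exact test is a conventional small-sample safety summary, keeps the patient as the unit of analysis, and is valid. Low power is expected in a study that calls itself pilot and exploratory, and no power is claimed for safety. All of this stands, and it is why the test should be kept. It does not explain leaving the visit data out of the stated analysis.

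Four stronger readings are tempting, and the article does not support them.

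- A reader might infer that the ever/never measure is bound to saturate. That needs a per-visit rate of roughly 10% or more with weak clustering. At 1 to 2% per visit only 14 to 26% of patients are ever affected; the power is then low because there are 10 per arm, and the rank test is weak too.
- A reader might infer that Fisher cannot show any doubling. If the proportion of patients affected doubles, its power is 25% at 40% v 80% and 62% at 50% v 100%. The 11% ceiling concerns doubled per-visit rates.
- A reader might infer that a non-significant test will be presented as proof of safety. No passage says so.
- A reader might infer that safety as a whole is reduced to one yes/no. That describes the stated analysis but not the collection, because serious events are recorded separately with relatedness.

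A final fair point is multiplicity: the Safety section names six tDCS effects, so tests by type should be treated as descriptive.

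**Conclusion.** The point holds as a weakness in a stated analysis; it is neither a contradiction nor an invalid test. The planned comparison leaves out information already collected at every treatment visit. For a doubled per-visit rate it has at most about 11% power across the settings tried, and close to none when side effects are common and visits nearly independent. Visit counts recover much of the loss when side effects are common: at 20% v 40%, 95% power with independent visits and about 35% at correlation 0.3. They recover little when side effects are rare, where 10 per arm is the limit under either test.

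These figures rest on assumed rates and correlations, a constant per-visit rate within each patient, and a two-sided 0.05 level. The counts needed for significance in step 1 rest on the last of these alone. A non-significant Fisher result could not by itself support the safety hypothesis.

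**What to change.** Keep the proportion of patients affected and the Fisher test. Add to the safety paragraph of Statistical and data analyses:

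1. For each recorded side-effect type, the number of treatment visits with the event per patient, summarised by arm, with the between-arm difference and its 95% CI and a patient-level rank or permutation test. State that these tests are descriptive and unadjusted across types.
2. Serious events as counts per arm with exact 95% CIs.
3. A sentence saying that any conclusion on the safety hypothesis will rest on these intervals and not on a non-significant test.

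The cost is a change of wording, slightly more analysis and several unadjusted descriptive comparisons. The data are already recorded at every visit, so nothing new has to be collected.

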**Methods/Design:**

In a randomized, sham-controlled, double-blinded pilot clinical study, patients with chronic stroke (n = 20) are assigned to receive transcranial direct current stimulation delivered to the premotor cortex or sham during rehabilitation of the paretic arm/hand. Patients receive the designated intervention for 30 min, twice a day for 3 days a week for 5 weeks. We assess hand function and patients’ reports of use of paretic hand. A general linear mixed methods model will analyze changes from pre- to post-intervention. Responders and non-responders will be compared upon baseline level of function, and neural substrates, including function and integrity of output tracts, bi-hemispheric balance, and lesion profile. Incidence of adverse events will be compared using Fisher’s Exact test, while rigor of blinding will be assessed with Chi-square analysis to ascertain feasibility.

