Use of chronic paradigms offers another important advantage, namely, retention. Besides the primary endpoint, we have built a delayed follow up. Initial clinical trials note that groups receiving cortical stimulation retain benefits whereas the ones receiving rehabilitation alone show a dip in performance after the end of training
[8,9]. These delayed benefits, maintained post-stimulation, may be indicative of a neuro-protective effect
[6] that we may be able to infer by completing our 3-month follow up.

Besides duration and retention, we suggest other potential advancements that could help improve the rigor of study design in the field. Creating a sham-controlled, double-blinded approach remains ethically and technically challenging with invasive stimulation
[8-10], and sham conditions created with noninvasive rTMS have not been strongly convincing either
[24,25]. Using tDCS may offer a unique opportunity to create a more valid sham for effective blinding
[62] and provide a better estimation of the placebo effect. Caveats remain to be addressed, however. Is it possible that what is gained in safety-feasibility with tDCS is lost in effectiveness, when relating to more focal methods such as rTMS and invasive cortical stimulation
[4].

Overall, the strengths of our pilot protocol include 1) examining a novel target of stimulation that differs from the classical and contemporary approach; 2) use of a generalizable rehabilitation paradigm that is delivered over the long term to generate true estimates of efficacy, adherence, and retention, thence, utility of brain stimulation; 3) use of a method of stimulation that is low cost, safe, feasible and allows estimation of the magnitude of the placebo effect; and 4) characterization of structural, pathologic, neurophysiologic and functional predictors of response. Despite these strengths, we anticipate challenges. The estimated sample size may be limited. Because others have noted significant effects with similar repeated-measures designs with a total of 14
[30] to 24

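### The three-visit interaction followed by Tukey HSD does not identify the 5-week UEFM effect on which the trial was sized

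*Protocol article*

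**What the plan says.** All places are in the protocol article.

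- **Abstract, Methods/Design:** "A general linear mixed methods model will analyze changes from pre- to post-intervention". Two time points are involved.
- **Sample size estimation and Figure 2 caption:** 10 per group gives 97% power for the group-by-time interaction, from 500 simulations. The caption says "The analysis was performed at a 0.05 significance level considering 2 × 2 factorial analysis of variance (ANOVA"), with the layout given as "tDCS plus CIMT and sham tDCS plus CIMT from pretest to post-test" and the remark "Power has been estimated here for an interaction term (A *C"). In a 2 × 2 layout that interaction has 1 degree of freedom and equals the between-arm difference in change at 5 weeks.
- **Study design and Discussion:** the 3-month visit is there to examine retention. The Discussion sets it apart: "Besides the primary endpoint, we have built a delayed follow up".
- **Statistical and data analyses, efficacy:** "A general linear mixed-model approach will be followed to analyze functional outcomes across three levels of time (pre, post, and follow-up"). Then: "Significant two-way interaction, whenever present, will be explored using the Tukey honestly significant difference (HSD) test". UEFM is the primary endpoint, but no deciding time point, model term or contrast is named.
- **Same section, markers of recovery:** responders are classified on UEFM gain after the 5 weeks of intervention.

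**The concern.** The article describes two different efficacy tests. The sized one asks whether the arms differ in change from pretest to post-test. The one in the analysis section asks whether the arms differ in their course over three visits. A significant answer to the second does not say where the difference lies.

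The only named next step is Tukey HSD. Applied in the usual way to the six group-by-visit means, it makes 15 pairwise comparisons, and none of them is a between-arm difference in change. Post-test tDCS against post-test sham takes no account of pretest, and pretest against post-test within one arm is not a treatment comparison.

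The trial could therefore report a significant interaction without a 5-week effect, or a significant interaction with no significant between-arm pair at post-test. The sample-size section says the pilot is meant to supply effect-size estimates for larger trials. An omnibus F test followed by cell-mean comparisons does not yield that estimate.

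**Working it through.** **Inputs.** From the article: 10 per arm, 1:1 allocation, significance level 0.05, 97% power for the 2 × 2 interaction, 500 simulations, and three visits in the analysis model. Not in the text: effect size, SD, visit-to-visit correlation ρ and sidedness. I assume two-sided tests, compound symmetry, and ρ from 0.3 to 0.95.

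**Step 1: the plan's own figure.** The 97% cannot be reproduced without an effect size and SD. Its simulation interval can be checked with exact binomial limits. 415/500 gives 79.41 to 86.19% and 498/500 gives 98.56 to 99.95%, both as printed. For the interaction, 486/500 (97.2%) gives 95.35 to 98.46%. The printed lower limit fits and the printed upper limit of 99.46% does not. That is a small separate point, and I take 97% as given.

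**Step 2: implied effect.** For a two-sample t test on change with 18 df, the noncentrality is d√(n/2) = d√5, with d in SDs of change and critical value 2.10. Power of 97% implies d = 1.818. As a smaller assumed effect, 80% power implies d = 1.325.

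**Step 3: the three-visit interaction.** Under compound symmetry, λ = (n/2)·Σ(δⱼ − δ̄)²/σ²w, where δⱼ is the arm difference at visit j and σ²w the within-patient variance. The SD of change is √2·σw, so λ = 10·d²·S. Here S is the sum of squares about its mean of the effect profile over pretest, post-test and follow-up, in units of the effect. The test is F(2, 36), critical value 3.26.

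| Profile (pre, post, follow-up) | S | λ and power at d = 1.818 | λ and power at d = 1.325 |
|---|---|---|---|
| 0, 1, 1 (fully retained) | 0.667 | 22.04; 98.6% | 11.70; 84.4% |
| 0, 1, 0.75 | 0.542 | 17.91; 96.1% | 9.51; 75.8% |
| 0, 1, 0.5 (half retained) | 0.5 | 16.53; 94.7% | 8.78; 72.2% |
| 0, 1, 0 (fully lost) | 0.667 | 22.04; 98.6% | 11.70; 84.4% |
| 0, 0, 1 (3 months only) | 0.667 | 22.04; 98.6% | 11.70; 84.4% |

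The 2 × 2 test has 97% and 80% at these two effects whenever the full effect is present at post-test. In the last row there is no 5-week effect, and a pretest-to-post-test contrast rejects in about 5% of trials. The interaction rejects in 98.6% or 84.4%.

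**Step 4: Tukey HSD on six cell means.** The critical value on the t scale is the studentized range for six means divided by √2. That is 4.25/√2 = 3.01 on 36 df and 3.18 on 18 df, against 2.10 for one contrast on 18 df. The post-test arm difference in SDs of the score itself is d√(2(1 − ρ)). At d = 1.818 this is 1.82, 1.41 and 0.81 for ρ = 0.5, 0.7 and 0.9. In 20,000 simulated trials per setting with a 5-week effect, the interaction and then the post-test pair were both significant as follows:

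| ρ | Between-patient error |
|---|---|
| 0.5 | 81 to 84% |
| 0.7 | 53 to 54% |
| 0.9 | about 12% |

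If the within-patient error were used, the range over these correlations would be 78 to 96%.

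**Step 5: one 5-week contrast adjusted for pretest.** The variance relative to a change score is (1 + ρ)/2, with 17 df.

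| ρ | Variance ratio | Power where change gives 97% | Power where change gives 80% |
|---|---|---|---|
| 0.3 | 0.65 | 99.7% | 93.3% |
| 0.5 | 0.75 | 99.3% | 89.7% |
| 0.7 | 0.85 | 98.6% | 85.7% |
| 0.9 | 0.95 | 97.5% | 81.7% |
| 0.95 | 0.975 | 97.2% | 80.7% |

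**The case against.** Several objections have force.

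- **A reader might infer that the plan wastes power.** The figures do not support that as a general claim. With the effect fully retained or fully lost, the three-visit interaction is slightly stronger than the 2 × 2 test (98.6% against 97%, or 84.4% against 80%). At the implied effect, half retention costs 97 − 94.7 = 2.3 points.
- **A reader might infer that baseline is ignored.** It is not. Pretest is a level of time, so the interaction already compares changes from baseline. What is absent is a named covariate, which a condensed article may leave to the analysis plan. Adjusting for pretest instead of using change is a gain in precision, not the correction of an error.
- **A reader might infer that the interaction alone decides efficacy.** The article does not say so. It also gives power for group and time, and the pretest-to-post-test contrast can be taken from the three-visit model (about 97.7% power on 36 df at the implied effect).
- **The Tukey family and error term are not defined.** The power figures in step 4 therefore show what could happen under stated assumptions. They are not a property of the plan.
- **An effect at 3 months only is an extreme case**, which the visit means would reveal. However, the Discussion itself expects arms to separate after training ends, because earlier trials saw rehabilitation-only groups decline. A contribution from follow-up is thus one the authors foresee.
- **This is an exploratory pilot** that leaves clear evidence of efficacy to larger trials. That lowers the severity.

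The conflict between stated passages remains: two visits in the abstract and sizing, three in the analysis, and no contrast that connects them.

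**Conclusion.** The point holds in limited form and should be fixed. The sized test (1 df, pretest to post-test) is not the analysis described (2 df, three visits), so the 97% does not describe the latter. Its power at the same 5-week effect runs from about 94.7% (half retained) to 98.6% (fully retained or fully lost). A significant three-visit interaction does not by itself show a 5-week effect: if the effect exists only at 3 months, it appears in 84% to 98.6% of trials.

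Tukey HSD in its usual form does not supply the missing contrast and uses a critical value of about 3.0 to 3.2 where one contrast needs 2.1. How much power that costs cannot be fixed from the article, because neither the correlation nor the error term is given.

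The power figures assume two-sided 5% tests and compound symmetry, with effects of 1.818 SD of change (implied by 97% power) or 1.325 SD (an assumed 80%). The Tukey critical values assume all six cell means are compared.

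**What to change.** 1. Name the tDCS-minus-sham difference in UEFM at the 5-week post-test, adjusted for pretest UEFM, as the single primary efficacy contrast. Test it two-sided at 5% and report the estimate with a 95% CI.
2. Take it from a mixed model with post-test and follow-up as outcomes, pretest UEFM as covariate, and arm, visit and arm-by-visit terms.
3. Report the 3-month contrast from the same model as secondary, for retention, with its 95% CI.
4. Do not use the omnibus interaction and Tukey HSD for the primary question.
5. Align the abstract, the sample-size section with its Figure 2 caption, and the analysis section on this contrast.

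The cost is wording and one degree of freedom for the covariate, with no new data. The gain in power is small if the pretest-to-post-test correlation is about 0.9 or higher: 80% becomes about 86% at 0.7 and 82% at 0.9. The trial is still enrolling, so the change can be made before results are known.
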